##### Qualitative method

We will use participatory aspects of the qualitative data collection to engage these various stakeholders as follows:

**Key Informants Interviews:** We will conduct interviews with the communities and facilities stakeholders to determine their views on PHCs and how to improve its use by women seeking pregnancy care. Those views will be incorporated in the design of the project implementation.

**Focus Groups Discussion:** We will also conduct focus groups discussion (FGDs) with various categories of women to elicit their views on PHCs and pregnancy care, and feedback such views into the planning and design of the intervention. In particular, we will seek ways during the FGDs to determine how to include women’s perspectives through all phases of the implementation process.

**Community Conversations:** We would hold initial community conversations (CC) with community leaders in the identified project communities. During CC, we will bring together the decision-makers and leaders in each community to a village hall meeting to discuss the project ideas and intentions. We will introduce the project objectives and request them to identify ways the communities would help to solve the problems. The idea behind community conversation is to ensure that the communities identify the problems themselves and proffer solutions that they themselves are comfortable with. This way, not only will the communities participate fully in the project activities, they would also owe the project and sustain its implementation over time.

**High Level Advocacy**: We will pay advocacy visits to policymakers/decision-makers identified above to explain the project objectives and activities and to ensure that they provide resources (both human and financial) to undertake the improvements of the project PHCs. We hope to conduct high-level advocacy to enable decision-makers and policy-makers to prioritise the improvement of PHCs.

#### Implementation tools

The formative study (Phase 1) will utilize Equitable Impact Sensitive Tool (EQUIST) and Knowledge Translation (KT) strategy. An Intensive training on EQUIST, a tool for high-impact intervention and budgeting will be conducted to teach team members on the strategies for knowledge translation on the project using EQUIST as a guiding model to address health systems bottlenecks hampering the delivery of maternal care services, potential improvement and cost implication needed for the expected results. EQUIST as a planning tool to improve maternal and child health is helpful to identify how disadvantaged rural women can be targeted to utilize Primary Health Centres (PHCs) for maternal and child health care. The analysis will also enable the identification of why women are disadvantaged, especially highlighting the gender and social equity dimensions. It will also include an analysis of how the combination of evidence-based high impact interventions and health system strengthening strategies can produce the best results for the project. Other skills to be taught at the training will equip project team members on productive knowledge translation strategies including inter-sectorial collaboration in policy making and implementation, managing political interference in policy making and implementation, policy formulation and how the legislation process can be leveraged to support and sustain the project. The Knowledge Translation Platform (KTP) will utilize production of policy briefs on maternal health, advocacy visits to key stakeholders and decision makers in the LGAs, Edo State Ministry of Health, Federal Ministry of Health, the health practitioners fora, print and electronic media, the local NGOs, the intervention communities’ partners, research publication, and West African Health Organization (WAHO). This list will be complemented if needed and according to the circumstances on the field.

#### Phase 2: Design and implementation of the intervention

##### Intervention design workshop

Following Phase 1, we will organize an intervention workshop to design the intervention using Phase 1 research findings. The intervention workshop will also serve to disseminate Phase 1 research findings so as to build support for the project among critical stakeholders.

##### Intervention design

The intervention will consist of 1) strategic approaches such as information provided to pregnant women to encourage them to attend primary health care and use family planning, antenatal, delivery and postnatal services; 2) targeted community health education and advocacy activities; 4) community maternal audit/accountability activities, with community-led activities aimed at promoting utilization of services; 4) outreach services by PHCs; 5) PHC strengthening including training of health providers on treatment protocols and referrals; 6) enumeration of traditional birth attendants and training/motivating them to refer maternal and child health cares; and 7) training and kitting of community health rangers who will be trained to follow up women at home to ensure that they do not default but that they continue to use PHC services until delivery.

#### Phase 3: Monitoring and evaluation of the intervention

WHARC has an existing Monitoring and Evaluation Department that would be used to monitor and evaluate the project. In brief, both process and outcome indicators will be used to monitor the achievements of the specific objectives of the project. A logic framework will be designed that will capture each research objective, the expected outcomes, the indicators for measurement, means of verification and the identification of the specific reporting project official. Both quantitative as well as qualitative measures will be used to capture the results of the project. Through triangulation of the qualitative and quantitative results, a more comprehensive assessment of the results of the project and the intervention will be obtained.

The indicators for measuring the success of the project are being identified at three levels: indicators for the formative research phase (Phase 1), indicators for the intervention phase (Phase 2), and indicators of the translational research phase.

### Data source and sampling

A combination of secondary and primary data is required for the study. The sample size formula below is applied for the formative research survey as follows:

n_1_ = {[p_1_q_1_ + p_o_q_o_]) (Z_α/2_ + Z_β_)^2^}/ (p_1_-po)^2^.

p_0_ = utilization of PHC for maternal and perinatal in the control arm (assumed to be − 5 reduction in the prevalence in the experiment site).

p_1_ = utilization of PHC for maternal and perinatal care in the experimental arm.

*z*_*α*_ = Two-sided standard normal variate at 95% level of significance = 1.96.

*z*_*β*_ = Statistical power at 80% = 0.84;

n_1_ = n_2_.

n_1_ = no of study participants in the experimental group.

n^2^ = no of study participants in the control group.

We assume 50% since there is no literature from the geographical location of the study which reported the prevalence of utilization of PHCs for maternal and perinatal health care. Thus;

n^1^ = (0.50 × 1–0.50 + 0.45 × 1–0.45) (1.96/2 + 0.84)^2^/(0.50–0.45) 2.

(0.25 + 0.2475) (3.3124)/0.0025.

n^1^ = 659.

n^2^ = 659.

Total sample size = 1318.

10% adjustment for non-response = 132.

Total = 1450.

There will be 725 respondents in the experiment LGA and 725 in the control LGA.

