**Methods:**

An open-labelled, randomized controlled trial will is carried out in two local government areas selected based on three criteria (i) maternal mortality rates (ii) PHC utilization rates and (iii) and geographic localization. The study will be conducted over 54-months in six communities, with PHCs in six communities of similar status serving as control sites. Surveys about quality of care and maternal health services utilization will be carried out at baseline, at midterm and at end of the project to test the effectiveness of the intervention, alongside conventional epidemiological measures of maternal and perinatal mortality. Ethical approval for the study has been granted (reference no. NHREC/01/01/2007). The findings will be published in compliance with reporting guidelines for randomized controlled trials.

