### Study design and setting

A community-based, multi-site, and multi-disciplinary cluster randomized trial using a mixed methods approach will be used. The project will be done in three phases: A formative phase (Phase 1) and an intervention phase (Phase 2), followed by evaluation of the intervention and policy transformation of the findings (Phase 3). The study will be conducted over 54-months in selected intervention communities, with selected communities of similar status serving as control sites. Surveys about maternal health services utilization will be carried out at baseline, at midterm and at end of the project to test the effectiveness of the intervention, alongside conventional epidemiological measures of maternal and perinatal mortality, each also collected in the three terms (Table 1).

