### Study phases

#### Phase 1: Formative research

##### Quantitative method

The quantitative instruments (individual woman, exit interview and site inventory assessment questionnaires) will be entered into a computer-assisted personal interviewing (CAPI) program. This method will explore the supply factors in the use or non-use of maternal health care services. A probabilistic sample will be carried out in the 20 communities to be selected out of a total of 142 communities in both LGAs, and will have two phases. In the first phase, 10 communities (5 PHC owned and 5 non-PHC owned communities) in each of the two LGAs will be chosen. All ever-married women aged 15 to 45 in each household to be visited who have an under-5 children will be eligible for interview to determine whether they have given birth within the period, and if so whether they have used the services of the PHC. This will continue until the required sample size of about 1450 women is achieved taking at least 72 women from each community. In addition, exit interview will be conducted in up to 10 selected health facilities with clients who would have received antenatal care, delivery or post natal care, to assess patients’ satisfaction through quality of care, patients’ time of travel or distance to facilities, and the cost of services at the PHCs.

In the second phase, PHCs/facilities assessment will be done through a checklist developed using the National Primary Health Care Development Agency standard. This will be used to assess the quality of infrastructural facilities, availability of clinical services through medical equipment and essential drugs as well as the availability of health care providers. All quantitative instruments will be designed and pre-tested to ensure that they are consistent to sufficiently answer related research questions.

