### Statistical analysis plan

Baseline data will be summarized using descriptive statistics and percentages. No hypothesis testing will be performed on baseline data. However comparability of the LGAs will be evaluated from the perspective of clinically meaningful differences. The primary outcome SBA will be analyzed. The outcome data will be aggregated to the cluster level and analyzed with regression model to examine the determinants of skilled pregnancy care using PHCs. The Statistical Package for Social Science (SPSS) version 22.0 (SPSS Inc., Chicago, IL, USA) will be used to enter and analyse the data.

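### The only power calculation is a two-arm comparison assigned to the pre-intervention formative survey, and its 80% is not delivered even if it is read as the trial's own

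*Protocol article*

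**What the plan says.** In the protocol article, *Data source and sampling* gives the only size and power calculation and names its target: "The sample size formula below is applied for the formative research survey as follows". The formula has an experimental-arm rate (0.50) and a control-arm rate (0.45), with the error rates given as "Two-sided standard normal variate at 95% level of significance = 1.96" and "Statistical power at 80% = 0.84". It arrives at 659 per group, 1,318 in total, and 1,450 after a 10% addition for non-response, split as 725 in each of two LGAs.

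The *Quantitative method* section under Phase 1 uses the same total for the formative survey: "A probabilistic sample will be carried out in the 20 communities to be selected out of a total of 142 communities", with 10 communities per LGA, half of them without a PHC. It adds: "This will continue until the required sample size of about 1450 women is achieved taking at least 72 women from each community".

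The intervention is designed afterwards, from the Phase 1 findings (*Intervention design workshop*). According to *Study design and setting*, the trial is cluster randomized, and surveys "will be carried out at baseline, at midterm and at end of the project to test the effectiveness of the intervention". The abstract gives the arms: "The study will be conducted over 54-months in six communities, with PHCs in six communities of similar status serving as control sites". *Statistical analysis plan* names SBA as primary outcome, aggregates outcome data to cluster level, and says of the first wave: "No hypothesis testing will be performed on baseline data".

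**The concern.** A two-arm formula with a power term answers one question: how many women are needed to detect a difference between arms. The text assigns it to a survey done before the intervention exists, so that survey cannot show an intervention effect. If it is also the baseline wave, the analysis section rules out testing on it.

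The comparison that does need the calculation differs in three respects: 12 communities rather than 20, randomized clusters rather than individual women, and SBA rather than PHC use. A reader will nevertheless take 80% as the power of the effectiveness comparison. If the real power is far lower, a null result could be misread as evidence against the intervention package.

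**Working it through.** **Inputs from *Data source and sampling*:** p1 = 0.50, p0 = 0.45, z = 1.96 (two-sided 5%), z for power = 0.84, and 659 per group (725 with the non-response addition). From the abstract: six and six communities. From *Quantitative method*: 1,450 women in 20 communities, which is 72.5 each. **Assumed:** an ICC of 0.01 to 0.05, since the document gives none.

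**1. The plan's own figure.** Variance term: 0.50 × 0.50 + 0.45 × 0.55 = 0.4975. The plan enters 1.96/2 = 0.98:

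- n = 0.4975 × (0.98 + 0.84)² / 0.05² = 0.4975 × 3.3124 / 0.0025 = 659.2
- 2 × 659 = 1,318, and 1,318 × 1.10 = 1,450

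The figure reproduces, but only with the halved value. The subscript α/2 already selects 1.96, so the halving is an error. A critical value of 0.98 corresponds to a two-sided alpha of about 0.33.

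**2. The same formula with 1.96.**

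- n = 0.4975 × (1.96 + 0.84)² / 0.0025 = 0.4975 × 7.84 / 0.0025 = 1,560 per group

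**3. Power at the planned size, before clustering.** Power = Φ(0.05 / √(0.4975/n) − 1.96).

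- n = 659: Φ(1.820 − 1.96) = 44%
- n = 725: Φ(1.909 − 1.96) = 48%

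**4. With clustering, all 1,450 women in the 12 trial communities.** Cluster size m = 1,450/12 ≈ 121; design effect = 1 + (m − 1) × ICC; divide 1.909 by its square root.

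| ICC (assumed) | Design effect | Power at 725 per arm |
|---|---|---|
| 0.01 | 2.2 | Φ(1.287 − 1.96) = 25% |
| 0.05 | 7.0 | Φ(0.721 − 1.96) = 11% |

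**5. With the survey's per-community number carried into 12 communities (an assumption).** 6 × 72.5 = 435 women per arm.

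| ICC (assumed) | Design effect | Power at 435 per arm |
|---|---|---|
| none | 1 | Φ(1.478 − 1.96) = 31% |
| 0.01 | 1.715 | 20% |
| 0.05 | 4.575 | 10% |

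The normal approximation is somewhat generous here. A cluster-level analysis with six clusters per arm would use a t reference with 10 degrees of freedom.

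**6. Does the primary outcome change this?** *Background* puts national SBA at under 33%. Taking 33% as an illustration, a 5-point difference at 659 per group has about 47% power (33% v 38%) or 50% (33% v 28%) before clustering. Changing the outcome does not restore 80%.

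**7. Detectable difference.** Holding the variance term at 0.4975, the difference detectable with 80% power is 2.80 × √(0.4975 × design effect / 725). This is about 7 points unclustered, 11 points at a design effect of 2.2, and 19 points at 7.0, against the planned 5.

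**The case against.** The strongest reply is that the word formative is a loose label. The same section speaks of experimental and control arms and ends with 725 women in each of an experiment and a control LGA. Ten communities per LGA at about 72 women match that split, and the surveys are to be repeated at midterm and end. On this reading the first wave was sized for the arm comparison and the later waves repeat it. Nothing in the article excludes this, and it stands as a possible intention. It does not save the 80%, which fails on that reading too (steps 2 to 4).

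Several further limits also stand:

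- A reader might infer that the 80% belongs to an analysis the plan forbids. That goes too far. Declining to test baseline data is ordinary practice and does not stop a trial from sizing its baseline wave for a later comparison. That the formative survey is the baseline wave is itself an inference, though a strong one.
- Most of the loss of power does not come from the label. The halved critical value takes 80% down to 44% at 659 per group, and clustering takes it lower. Only the step from 48% to 31% reflects 20 survey communities against 12 trial communities, and it rests on an assumed end-of-project size.
- The absence of a number of women for the end-of-project survey, or of a precision statement for the formative survey, is something a condensed article may leave to the full protocol. Neither is counted as a fault here.
- The sampling section describes the arms as LGAs and the abstract describes them as communities. The working uses the abstract's six and six.

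**Conclusion.** The point holds in a limited form. A two-arm power calculation is assigned in writing to a pre-intervention survey, while the effectiveness comparison has a different set of communities, a clustered design and a different outcome. On no reading of the text is the stated 80% delivered. Before clustering, power is about 44% to 48% at the planned size. It is about 25% to 11% if all 1,450 women come from the 12 trial communities. If only about 72 per community are taken there, it is 31% before clustering and 20% to 10% after. The clustered figures depend on the assumed ICC range, and the last set also on the assumed number per community. The figures of 44% and 48% need neither assumption.

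A reader might conclude that the effectiveness comparison was never sized at all. The document does not establish that: the arm-based formula may have been meant for it. This should be fixed, together with the critical-value and clustering errors in the same calculation.

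**What to change.** In *Data source and sampling*:

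1. State that the two-arm calculation refers to the end-of-project comparison in the allocated clusters, not to the formative survey.
2. Use 1.96 rather than 1.96/2, and include a design effect with a stated ICC or a range.
3. For SBA, the primary outcome, restate the power or detectable difference that the planned number of women and clusters delivers. If PHC use is kept as the basis, say why.

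A precision statement for the formative survey would be a useful addition but is optional.

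The cost is wording and restated figures, with no extra enrolment. The downside is a less favourable stated power: the rewording makes the claim correct but does not make the trial larger.

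### The sample-size calculation halves a critical value that is already two-sided, so 659 women per arm gives about 44% power for 50% v 45%, not 80%, even before clustering

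*Protocol article*

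**What the plan says.** The protocol article, section Data source and sampling, sizes a comparison of PHC use between an experimental and a control arm. The formula is "n_1_ = {[p_1_q_1_ + p_o_q_o_]) (Z_α/2_ + Z_β_)^2^}/ (p_1_-po)^2". Its inputs are:

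- Critical value: "Two-sided standard normal variate at 95% level of significance = 1.96".
- Power: "Statistical power at 80% = 0.84".
- Experimental-arm proportion, 0.50: "We assume 50% since there is no literature from the geographical location of the study".
- Control-arm proportion, 0.45: "assumed to be − 5 reduction in the prevalence in the experiment site".

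The substitution then reads "1.96/2 + 0.84)^2^/(0.50–0.45) 2" and the next line "0.25 + 0.2475) (3.3124)/0.0025". The section arrives at 659 per arm and 1,318 in total, adds 132 for 10% non-response to reach 1,450, and splits this as 725 in each of the two local government areas. The Phase 1 section, Quantitative method, turns the result into a recruitment target: "This will continue until the required sample size of about 1450 women is achieved taking at least 72 women from each community".

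**The concern.** In the printed formula it is α that is halved, and 1.96 is the normal quantile that results from halving a 5% α. The worked line halves the quantile itself, so the two-sided split is applied twice, the second time to the wrong quantity. The multiplier 3.3124 in the following line equals 1.82 squared, so 0.98 was really used in the arithmetic and the division by two is not a misprint.

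If so, the claim of 80% power for a 5-point difference is false on the plan's own inputs. A comparison of this size would miss a true 5-point difference more often than it found it, and a null result could be read as absence of effect. Any later inflation for clustering that started from 659 would start from less than half the right base.

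**Working it through.** **Inputs, all from Data source and sampling:** p1 = 0.50, p0 = 0.45, two-sided z = 1.96, power z = 0.84, equal arms, 10% added for non-response.

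**1. Reproducing the printed figure**

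- Variance term: 0.50 × 0.50 + 0.45 × 0.55 = 0.25 + 0.2475 = 0.4975.
- Multiplier as used: (1.96/2 + 0.84)² = (0.98 + 0.84)² = 1.82² = 3.3124.
- n = 0.4975 × 3.3124 / 0.05² = 659.2 per arm, printed as 659.
- 2 × 659 = 1,318; 10% is 132; the total is 1,450, or 725 per area.

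The printed chain is reproduced exactly, but only with 0.98.

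**2. The same formula with the declared critical value**

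- Multiplier: (1.96 + 0.84)² = 2.80² = 7.84.
- n = 0.4975 × 7.84 / 0.0025 = 1,560 per arm, or 3,120 in total. With the plan's own 10% addition, 3,120 + 312 = 3,432.
- 659 / 1,560 = 0.42.

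**3. Whether a standard variant gives 659**

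| Method (50% v 45%, 80% power) | n per arm |
|---|---|
| Unpooled, two-sided 5%, rounded z | 1,560 |
| Unpooled, two-sided 5%, exact quantiles | 1,562 |
| Pooled, two-sided 5% | 1,565 |
| Arcsine, two-sided 5% | 1,565 |
| Continuity-corrected, two-sided 5% | about 1,605 |
| One-sided 5% | 1,230 to 1,233 |

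None does. A critical value of 0.98 corresponds to a two-sided α of 0.33.

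**4. Power actually obtained, women independent**

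- At 659 per arm: SE = √(0.4975/659) = 0.02748; 0.05/0.02748 = 1.820; Φ(1.820 − 1.96) = Φ(−0.140) = 0.444. The pooled form gives 0.443 and the continuity-corrected form 0.422.
- At 725 per arm (every woman responds): SE = √(0.4975/725) = 0.02620; 0.05/0.02620 = 1.909; Φ(−0.051) = 0.480. The continuity-corrected form gives 0.458.
- A one-sided 5% test would give 0.569 at 659 and about 0.60 at 725.
- Check: Φ(1.820 − 0.98) = Φ(0.84) = 0.80, so the stated 80% is recovered only with the wrong critical value.

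**5. Difference detectable with 80% power, one arm at 50%**

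With p0 = 0.50 − d, the variance term is 0.5 − d². Setting (0.5 − d²) × 7.84 / d² = n gives d² = 3.92 / (n + 7.84).

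- n = 659: d² = 3.92/666.84 = 0.00588, so d = 0.0767, about 7.7 points (50% v 42.3%).
- n = 725: d² = 3.92/732.84 = 0.00535, so d = 0.0731, about 7.3 points.

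**6. Direction of the clustering effect**

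The section Study design and setting describes a cluster randomised trial, and the calculation contains no design effect. The power values above are therefore upper bounds, while 1,560 and the detectable differences are lower bounds. As an illustration only, take 72 women per community and an intracluster correlation of 0.01 to 0.05. The article gives no correlation, so this range is an assumption. The design effect is 1 + 71 × 0.01 = 1.71 up to 1 + 71 × 0.05 = 4.55, and power at 659 per arm falls from about 44% to between 28% and 13%.

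**The case against.** The strongest objection concerns scope. The article labels this calculation as belonging to the formative survey, which precedes the design of the intervention and cannot itself show an intervention effect. The Statistical analysis plan section rules out hypothesis tests on baseline data, names skilled birth attendance as the primary outcome and analyses it at cluster level. On this view 44% is not the power of any test the article says it will run on these 1,450 women, and it is certainly not the power of the primary analysis.

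Part of this stands. The 44% corrects the printed calculation; it does not estimate the trial's power. The link to the effectiveness comparison is also partly an inference, because the sizes of the midterm and end surveys are not given. The 50% is a convention adopted for want of local data, so the detectable difference depends on it.

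The error remains. The calculation defines its proportions by experimental and control arm, claims 80% power, and divides the women between an experiment area and a control area. It is the only sample-size justification in the article and it fixes the Phase 1 recruitment target. Study design and setting says that utilisation surveys at baseline, midterm and end will test effectiveness. If the survey were purely descriptive, the power statement would still be wrong. Nor is this a detail left to a fuller document: the contradiction is between lines printed in the same section.

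**Conclusion.** The concern holds. On the plan's own inputs (50% v 45%, two-sided 5%, 80% power, independent women) the requirement is 1,560 per arm, and 1,560 to about 1,605 across the usual two-sided formulas. The printed 659 is 42% of that. It gives about 44% power (42% to 44% across formulas), or about 48% (46% to 48%) if all 725 per arm respond, and it detects about 7.7 points, or 7.3 points at 725, with 80% power. The result does not depend on the choice of formula or on sidedness. It needs no outside figure. Clustering is a separate matter and can only make the position worse.

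**What to change.** Correct the worked line in Data source and sampling to (0.25 + 0.2475)(1.96 + 0.84)² / 0.0025 = 1,560 per arm, and withdraw the statement that 659 per arm, or 1,450 in total, has 80% power for 5 points.

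If the sample stays at 1,450, state either about 44% power for 50% v 45% at 659 evaluable women per arm, or a detectable difference of about 7.7 points (50% v 42.3%) at 80% power. Say that both assume independent women, so that the power is a ceiling and the detectable difference a floor. State also whether the calculation serves only the formative survey or the later effectiveness comparison too. Use 1,560, not 659, as the base for any design effect or other adjustment.

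The cost is a rewritten paragraph and a less favourable stated power; no extra women are needed. Keeping the 5-point, 80% target instead would mean 3,432 women with the plan's 10% addition, against 1,450, before any allowance for clustering.

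### The sample size for a cluster randomised trial treats women as independent and also halves 1.96: power for 50% v 45% is about 44% before clustering and, at an assumed ICC of 0.01-0.10, about 21%-8% with six communities per arm, not 80%

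*Protocol article*

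**What the plan says.** All references are to the protocol article.

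- **Design.** Study design and setting: "A community-based, multi-site, and multi-disciplinary cluster randomized trial using a mixed methods approach will be used".
- **Number of communities.** Abstract, Methods: "The study will be conducted over 54-months in six communities, with PHCs in six communities of similar status serving as control sites". That is 6 v 6.
- **Analysis.** Statistical analysis plan: "The outcome data will be aggregated to the cluster level".
- **Survey sample.** Phase 1, Quantitative method: "A probabilistic sample will be carried out in the 20 communities to be selected out of a total of 142 communities in both LGAs", with "taking at least 72 women from each community".
- **Sample size.** Data source and sampling: "The sample size formula below is applied for the formative research survey as follows". The formula compares two independent proportions, 0.50 in the experimental arm and 0.45 in the control arm, at two-sided 5% and 80% power. It gives 659 per group: "Total sample size = 1318". Adding 10% for non-response gives 1450, split as 725 in an experimental LGA and 725 in a control LGA.

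Every step is printed. None contains an ICC, a design effect or a number of clusters.

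**The concern.** The intervention acts on communities and their PHCs. Women in one community share the same facility, staff and transport, so their use of care is correlated. A sample of 66 to 121 women per community therefore carries less information than the same number of unrelated women. A formula for independent women does not give the power of the cluster-level comparison that the article names.

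The printed arithmetic has a second fault. The quantile 1.96 is already the two-sided value, yet it is divided by 2 before use.

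At stake is how the result is read. The project is meant to inform national policy. If the trial could not have detected the planned 5-point gain, a null result could be taken as evidence that the package does not work.

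**Working it through.** **Inputs from the article.** p1 = 0.50, p0 = 0.45, difference 0.05; z values 1.96 and 0.84; 659 per arm (725 with the non-response allowance); 6 communities per arm (Abstract), or 10 per LGA in the Phase 1 survey.

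**Assumed.** ICC 0.01 to 0.10, for illustration; equal cluster sizes; an unadjusted comparison at endline.

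**Step 1: the article's figure.** Variance sum = 0.50×0.50 + 0.45×0.55 = 0.4975. The z term used is (1.96/2 + 0.84)² = 1.82² = 3.3124. Then n = 0.4975 × 3.3124 / 0.0025 = 659.2. Twice 659 is 1318, and 1318 × 1.10 = 1449.8. All the printed figures reproduce, but only with 1.96 halved.

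**Step 2: without the halving.** n = 0.4975 × (1.96 + 0.84)² / 0.0025 = 0.4975 × 7.84 / 0.0025 = 1560.2, or about 1,562 per arm with unrounded z values.

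Power at 659 per arm with independent women: SE = √(0.4975/659) = 0.02748, and 0.05/0.02748 = 1.820. Power = Φ(1.820 − 1.96) = 44%. At 725 per arm it is 48%.

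**Step 3: add clustering.** With m women per community, DE = 1 + (m − 1) × ICC and SE = √(0.4975 × DE / n). Power is from a noncentral t with 2k − 2 degrees of freedom (k communities per arm) and noncentrality 0.05/SE. Detectable difference = (t for two-sided 5% + t for 80% power) × SE, where the t sum is 2.228 + 0.879 = 3.107 on 10 df.

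Six communities per arm, 659 per arm, m = 109.8:

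| ICC | DE | SE | Power for 5 points | Detectable difference |
|---|---|---|---|---|
| 0.01 | 2.09 | 0.0397 | 21% | 12 points |
| 0.02 | 3.18 | 0.0490 | 15% | 15 points |
| 0.05 | 6.44 | 0.0697 | 10% | 22 points |
| 0.10 | 11.88 | 0.0947 | 8% | 29 points |

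If all 725 per arm responded, power would be about 22% to 8%.

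If the 20 survey communities were the clusters (10 per arm, m = 65.9, 18 df), DE is 1.65, 2.30, 4.25 and 7.49 at the same ICCs, and power is 27%, 21%, 13% and 10%.

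**Step 4: separate the two errors.** Correct only the 1.96/2, to 1,562 per arm in 6 v 6 communities (m = 260.3). DE becomes 3.59 at ICC 0.01 and 26.93 at ICC 0.10, and power is 27% to 8% (t, 10 df). So correcting the z value does not repair the calculation. Nor would a design effect applied to 659, because 659 is already too small for independent women.

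**The case against.** **The calculation is only for the formative survey.** The article labels it so, and Phase 1 uses the same 1450. The label does not dispose of the point. The formula defines experimental and control arms, sets 80% power for the difference between them and allocates women to each. It is the only sample size given, and repeated surveys are the stated means of testing effectiveness. A survey of at least 72 women in each of 20 communities is itself clustered. The ambiguity should still be acknowledged and resolved.

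**Clustering alone takes power from 80% to these values.** A reader might infer this, but the printed figures do not support it. The fall from 80% to about 44% comes from halving 1.96. Clustering accounts for the further fall from 44%.

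**The trial has 20 clusters.** A reader might also infer this. The 20 are Phase 1 survey communities, half of them without a PHC, and are not stated to be randomised. The stated trial count is 6 v 6, so that case leads here.

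**The ICC is not from the article.** True; the range is an assumption. At a smaller ICC of 0.005, power at 659 per arm is still only 26% (6 per arm) or 32% (10 per arm) by t.

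**More women per community could never rescue 5 points.** This goes too far. For an unadjusted endline comparison of 6 v 6 communities, unlimited women still leave a detectable difference of 3.107 × √(0.4975 × ICC / 6), about 9 points at ICC 0.01. But baseline surveys are planned. Adjusting for cluster baseline values scales this by √(1 − r²). At an assumed r of 0.7 to 0.9, 9 points becomes about 6.4 to 3.9. The article does not specify such an adjustment, so this limits the claim without removing the problem.

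**Each arm may be one LGA.** The split into an experimental and a control LGA suggests it, while the design statement and the 6 v 6 count point to communities. The article does not settle which. With one LGA per arm, no cluster-level power figure applies, including those above.

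**Conclusion.** The concern holds in this form. The printed calculation does not give 80% power for 50% v 45%, for two independent reasons: 1.96 is halved, and clustering is ignored in a trial described as cluster randomised and analysed at cluster level. Since every step is shown, this is a misstatement in the article and not a detail left to a fuller document.

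Power is about 44% with independent women. It is about 21% to 8% with six communities per arm, on the assumed ICC of 0.01-0.10 and a t reference with 10 df. The exact value depends on that ICC, on equal cluster sizes and on no baseline adjustment. The conclusion that 80% is not reached at 659 per arm needs none of these, because it already fails with independent women. All the cluster figures presuppose that communities, not LGAs, are the randomised units.

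**What to change.** 1. Use 1.96, not 1.96/2, in the formula.
2. Multiply the variance by 1 + (m − 1) × ICC, use a t critical value with (clusters − 2) degrees of freedom, and state the number of clusters and women per cluster.
3. Estimate the ICC from the baseline survey, and show results over a range because one survey estimates it imprecisely.
4. Remove the claim of 80% power for 5 points. State instead the detectable difference for the fixed 6 v 6 communities: about 12 to 29 points at ICC 0.01-0.10 for an unadjusted endline comparison, smaller if cluster baseline values are adjusted for. If that adjustment is intended, say so.
5. Say whether the calculation serves the formative survey, the trial comparison or both.
6. Reconcile the LGA-per-arm wording with randomisation of communities.

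The cost is a recalculation, a revised protocol statement and a less favourable stated power. No extra participants or clusters are needed to make the statement correct.
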